**Recruitment rate**
Calculated by dividing the total number of participants recruited throughout the study by the number of months recruitment occurred.Objective: Based on clinical estimates of eligible individuals, approximately 3 to 4 participants were recruited each month.
**Retention rate**
Calculated by comparing the number of participants who complete baseline e-questionnaires to the number of participants who complete study exit e-questionnaires.Objective: Of participants who begin the study, ≥45% complete the study, and reasons for dropout are documented if participants wish to share [39,50].
**Response rate to study e-questionnaires**
Determined by the number of completed follow-up e-questionnaire assessments for participants who complete the study.Objective: Of participants who complete the study, ≥70% complete outcome measures across all time points. This is slightly higher than the 60% minimum required by biomedical journals [51], typical for web-based questionnaires and patient acceptability and satisfaction research [52,53].
**Uptake of intervention**
Nature of intervention access (modality, topics, and time points). Uptake of the intervention will be assessed by the number of participants who access the platform, and the number of times each modality was accessed throughout the study duration.Objective: Of participants in the experimental group, ≥85% will access at least one intervention modality [54,55].

**Table 2 table2:** Constructs and definitions of acceptability [35] as well as questions asked at baseline and exit [56].

Construct of acceptability	Definition	Question at baseline	Question at exit
Intervention burden	Perceived amount of effort required to participate in the intervention	Do you anticipate the amount of time you will spend reading and watching video or videos in this study will be acceptable?	Was the amount of time you spent reading the information on the e-handouts acceptable? Was the amount of time you spent watching the video or videos acceptable? How easy was it for you to access and use the information and support offered in the study? (overall)
Intervention coherence	Extent to which participant understands the intervention and how it works	—^a^	How understandable was the information in the e-handouts? How understandable was the information in the videos?
Perceived effectiveness	Extent to which the participants perceive the intervention as likely to achieve its purpose	How helpful do you anticipate the information and support offered in this study will be in helping you manage your treatment? (treatment management) How helpful do you anticipate the information and support offered in this study will be in reminding you to take your medication? (reminders)	How helpful was the information and support offered in this study in helping you manage your treatment? (treatment management) How helpful was the information and support offered in this study in reminding you to take your medication? (reminders)

^a^Not applicable.

#### Medication Adherence Self-Efficacy

The Medication Adherence Self-Efficacy Scale (MASES) [58] asks about participants’ level of confidence in taking their medication. The original scale contains 25 items, each rated from 1 (not at all sure) to 3 (extremely sure), with a total score calculated by summing the responses. Initially developed within the context of antihypertensive medication, the scale has been modified and adapted into 24-items for oncology oral agents [33]. For this study, 4 items were removed, and 20 items were used. The 4 items removed were not deemed suitable for the study as they pertain to taking the medication for the rest of their life, coming home late from work, being in a public area, and being afraid of becoming dependent on the medication.

#### Medication Adherence via Proportion of Days Covered

Participants were asked to provide the name and telephone number of their pharmacy, as well as consent for the research team to contact the pharmacy for records to calculate the proportion of days covered (PDC), in order to obtain the average adherence of each participant over 5 cycles of OAAs. PDC is defined as the “sum of the days” supply for all fills of a given drug in a particular time period, divided by the number of days in the time period” [59]. PDC is preferred over the medication possession ratio as the medication possession ratio can overestimate adherence for patients who refill their prescriptions early [59]. PDC will be assessed as the mean PDC for each group.

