A Canadian survey conducted among individuals treated for cancer in the last 6 months (N=3300), for instance, found that only 62% of individuals on OAAs reported receiving information and guidance on potential side effects and how to manage them, compared to 74% for radiation and 76% for intravenous chemotherapy. In the same sample, only 67% of individuals on OAAs felt their care provider did everything they could to help with side effects, compared to 73% for radiation and 76% for intravenous chemotherapy [14]. Elsewhere, the lack of OAA information and monitoring for side effects were found to be significantly related to fatigue, nausea and vomiting; change of taste; and poorly managed mouth sores [15].

Medication adherence, the extent to which a person’s medication-related “behavior corresponds with agreed-upon recommendations from their health care provider” [16], denotes a collaborative relationship between the health care provider and patient where the patient plays an active role in taking their prescribed treatment [17]. Medication adherence is construed as one of the primary determinants of treatment success, as unwanted alterations in dose and timing affect treatment-related outcomes [18,19]. However, medication adherence rates for OAAs vary significantly, with a systematic review across 63 studies reporting adherence rates ranging from 46% to 100% [20]. Lower OAA adherence is found to be related to decreased treatment effectiveness, increased health care utilization, and increased costs due to more physician visits, higher hospitalization rates, longer hospital stays, and in some cases, decreased survival [21-24].

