#### Follow-up Calls From Oncology Nurse

Participants in the experimental group can receive a call from the oncology nurse specific to their tumor site. A participant may request a phone call at each follow-up e-questionnaire by selecting “I would like to receive a phone call from a nurse” and identifying the topic they would like to discuss. The study coordinator forwards the participant’s name and contact number to the nurse. The participant’s symptom scores from the e-questionnaire are shared with their nurse at this time. The nurse calls the participants and speaks to them on the topic of their choice, and the interaction is documented in the patient chart as a virtual encounter.

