### Data Collection

In both groups, follow-up e-questionnaires were completed every week for the first month and 2 weeks for the following 4 months, or until treatment was completed (if less than 5 months). Given the considerable variability in the duration of time patients may remain on OAAs, the study duration of 5 months was established as a long enough period in consultation with medical oncologists and pharmacists and was deemed appropriate for assessing the primary outcomes of feasibility and acceptability. Participants were monitored more closely during the first treatment cycle, as this period is critical for identifying potential toxicities and making necessary dosage adjustments. Furthermore, it is crucial to establish positive medication adherence behaviors early in the treatment process [46]. After 5 months or until OAA treatment was completed (if less than 5 months), participants completed the exit questionnaire, and a subset of participants in the experimental group (n=10) and control group (n=10) who had completed the study were invited to participate in a semistructured interview.

All e-questionnaires were completed on Qualtrics, a secure web-based electronic data capture system licensed through McGill University [47]. A data management plan between the university and the affiliated hospital was established for the study (Multimedia Appendix 1). Details of each measure and timepoint are provided in Table 1.

Baseline questionnaires completed by all participants included sociodemographic and medical characteristics, cancer information-seeking preferences, and OAA knowledge.

**Table 1 table1:** Study data collection.

Objective and measure			Instrument		Items, n		Time of collection				
						Baseline		Weekly for the first cycle	Every 2 weeks for cycles 2-5	Final questionnaire	Study completion

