#### Medication Adherence via the Medication Adherence Report Scale

The Medication Adherence Report Scale (MARS-5; [name]) [60] is a validated measure of medication adherence, with a Cronbach α of 0.67 [60,61]. It is the shorter version of the MARS-10. MARS-5 contains 5 items, each rated from 1 (always) to 5 (never). Total scores range from 5 to 25. In addition, participants are asked specifics about their OAA regimen such as timing, dose delays, interruptions, and stoppages [62].

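### PDC as defined scores days on a provider-ordered hold as non-adherence, against the article's own definition of adherence; any resulting bias between arms has no predictable direction

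*Protocol article*

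**What the plan says.** The section on PDC defines it as the total, in days, of "supply for all fills of a given drug in a particular time period, divided by the number of days in the time period". The data are pharmacy records, collected "in order to obtain the average adherence of each participant over 5 cycles of OAAs", and "PDC will be assessed as the mean PDC for each group". Data Analysis compares the two means at study completion by a 1-tailed independent-samples t test and correlates PDC with MARS-5. Table 1 gives chart review as the source for PDC.

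Four other places bear on this:

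- The Background defines adherence as the extent to which a person's medication-related "behavior corresponds with agreed-upon recommendations from their health care provider".
- Data Collection says of the first treatment cycle that "this period is critical for identifying potential toxicities and making necessary dosage adjustments".
- The MARS-5 section adds that "participants are asked specifics about their OAA regimen such as timing, dose delays, interruptions, and stoppages". Nothing in the article connects those answers to PDC.
- Follow-up Calls From Oncology Nurse gives experimental participants the option to request a call. When they do, the participant's "symptom scores from the e-questionnaire are shared with their nurse at this time".

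**The concern.** The definition of adherence and the PDC formula disagree about a patient who stops for two weeks because the provider said so. Under the Background definition that patient is adherent. Under the formula the patient has two weeks uncovered. The article expects dosage adjustments and asks about interruptions, so the case is foreseeable.

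PDC is the only adherence outcome that does not rest on self-report. If ordered holds are equally common in both arms, they lower both means and add noise. If they are not, part of the difference in mean PDC reflects prescribing and not patient behaviour. The planned correlation with MARS-5 could also be affected, because obeying a hold lowers PDC without any lapse for the patient to report. That effect has not been quantified.

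**Working it through.** **The plan's own figures.** The article states no PDC figure. Its sample size (36, raised for 30% attrition: 36/0.70 = 51.4, so 52) was derived for the repeated-measures ANOVA. It reproduces and does not depend on PDC.

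**Inputs from the article.** Five cycles; reminder templates of 21 and 28 days, hence windows of 5 × 21 = 105 or 5 × 28 = 140 days; final sample 23 experimental and 18 control.

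**Assumptions (not in the article).** Ordered holds of 7 to 28 days; each fill credited with the full cycle it serves; supply credited only for days inside a fixed window; a hold delays the next fill by its own length; no other missed doses.

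**Step 1, one patient with an ordered hold.** PDC = (W − h)/W, so the loss is h/W.

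| Hold h | W = 140 | W = 105 |
|---|---|---|
| 7 days | 0.05 | 0.067 |
| 14 days | 0.10 | 0.133 |
| 28 days | 0.20 | 0.267 |

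With h = 14 and W = 140, PDC is 126/140 = 0.90. With the hold days out of the denominator it is 126/126 = 1.00.

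If a delayed cycle lengthens the window instead, PDC = W/(W + h). For W = 140 this gives 140/147 = 0.952, 140/154 = 0.909 and 140/168 = 0.833. The losses shrink slightly but remain.

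**Step 2, ordered reductions.** PDC counts days of supply, not dose.

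- Reduced dose dispensed as a new fill with the same days' supply: 140/140 = 1.00, no loss.
- Stock already in hand is stretched: a 28-day fill that lasts 56 days leaves 28 days uncredited, so (140 − 28)/140 = 0.80. With an assumed 25% reduction just after the fill, it lasts 28/0.75 = 37.3 days. The extra 9.3 days cost 9.3/140 = 0.067 over the window.

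**Step 3, between arms.** If a proportion q more patients in one arm have an ordered hold, the difference in means shifts by q × h/W against that arm. For q = 0.10 to 0.30 and h = 7 to 28:

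- W = 140: 0.10 × 7/140 = 0.005 to 0.30 × 28/140 = 0.06.
- W = 105: 0.10 × 7/105 = 0.007 to 0.30 × 28/105 = 0.08.
- q = 0 gives no shift. An excess in the control arm gives the same sizes in favour of the intervention.

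**Step 4, effect on the planned test.** One-tailed t test, 23 v 18, with assumed alpha 0.05 and true difference 0.10:

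| Assumed SD | No bias | Bias −0.02 | Bias +0.02 |
|---|---|---|---|
| 0.10 | 0.93 | 0.80 | 0.98 |
| 0.15 | 0.67 | 0.51 | 0.80 |
| 0.20 | 0.47 | 0.35 | 0.59 |

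**The case against.** **A condensed article.** The formula is a generic definition taken from a cited source, and rules for holds could sit in a full protocol or analysis plan. That is fair for operational detail. But the article prints the formula, the group summary and the test, and the formula as printed gives the wrong value for a patient who obeys a hold. It prefers PDC to the medication possession ratio because the latter can overestimate adherence; it does not consider error in the other direction.

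**Bias against the intervention.** A reader might infer that nurse calls lead to more holds in the experimental arm, so that PDC is biased against it by design. The documents do not support this. The participant chooses the topic of the call, and nothing says that a call results in a hold or reduction. Both arms keep oncologist, pharmacist and nurse contact under usual care. The trial also hypothesises lower symptom distress in the experimental arm, which could mean fewer holds there and a bias in its favour. Only the possibility of a difference stands.

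**All dose reductions.** A reader might also infer that every reduction lowers PDC. Step 2 shows that only stretched stock does.

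**Limited stakes.** Feasibility and acceptability are the primary outcomes, PDC is one of several measures of potential effects, and the sample size does not rest on it. This stands, and it keeps the point modest.

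**The correction has its own weakness.** The regimen questions are not said to record exact dates or who ordered an interruption. Nurse calls are charted, so holds could be better documented in the experimental arm. This stands and shapes the fix.

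**Conclusion.** The point holds as a fault of measurement: the printed PDC rule counts ordered-hold days, and days on stretched stock after an ordered reduction, as non-adherence. That contradicts the article's own definition of adherence, and the article anticipates such changes.

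For one fully adherent patient, the loss is 5 to 20 points over 140 days for an assumed hold of 7 to 28 days, on the crediting assumptions listed above. Between arms, the bias is zero if holds are balanced. Under the assumed imbalances it is 0.5 to 6 points (140 days) or 0.7 to 8 points (105 days), of either sign. Hold rates, hold lengths and the PDC standard deviation are all assumed, so these figures show scale and are not estimates for this trial. A correction is worth making because it is cheap; the feasibility and acceptability conclusions are unaffected.

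**What to change.** Define PDC against the regimen as recommended at the time, with one rule for both arms, applied blind to arm where possible:

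- Remove provider-ordered hold days from the denominator, and carry the supply unused during the hold forward. If calendar days are merely deleted, the late refill still shows as a gap.
- From the date of an ordered change, re-express the remaining stock in days at the dose then recommended.
- Take holds and change dates from the chart review listed in Table 1 and from pharmacy records, with the regimen answers collected alongside MARS-5 as support.
- Report PDC as now defined next to it as a sensitivity result.
- Tabulate ordered holds and reductions by arm, so that readers can see whether they differ and in which direction.

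The cost is one derivation rule and some chart abstraction, with no change to the sample size. The downside is dependence on charted dates, whose completeness may differ by arm because nurse calls are charted; the unadjusted result shows how much turns on this. The change concerns how adherence is measured and implies nothing about when doses should be held or altered.

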#### Medication Reminders

Participants can receive daily e-reminder notifications on their smartphones to take their OAA medication (Figure 4). The e-reminders use preconfigured templates tailored to a 21-day cycle (14 days on per 7 days off) or a 28-day cycle (21 days on and 7 days off) that users must select, with options for once or twice daily reminders. Upon the conclusion of each cycle, users receive a notification prompting them to refill their prescription and reload the 21-day or 28-day cycle template.

In sum, the study intervention was designed to increase SE for OAA adherence through direct mastery experiences (self-management and reminders), vicarious experiences (video), verbal persuasion (phone calls), and feedback (self-management and reminders).

Participants in the control group continued to receive care as usual. This includes follow-up care with their oncologist, contact with their pharmacist and nurse as needed, as well as access to any internal and external supportive services from other health care professionals (eg, psychosocial oncology, social services, physiotherapist, occupational therapist, etc).

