### Data Analysis

Statistical analyses to be performed rely on Microsoft Excel, SPSS (version 25; IBM Corp) [65], and R (R Project for Statistical Computing) software [66]. For PDC, independent sample 1-tailed *t* tests will be performed to calculate the difference between 2 independent means of the experimental and control groups at one time point—study completion. Changes over time in MARS-5, MASES, and ESAS-r will be assessed using repeated-measures ANOVA. Between-group analyses will be conducted to examine how each group changed over time, and within-group analyses will be conducted to examine how participants changed over time.

The relationship between objective (PDC) and subjective (MARS-5) measures of medication adherence will be assessed using Spearman correlation coefficients. Oral chemotherapy knowledge at baseline and study exit will be compared using paired sample 1-tailed *t* tests.

Interviews were conducted individually, audio recorded, and transcribed verbatim by the first author, a doctoral candidate at the time with experience in qualitative research in oncology working on her dissertation. A reflexive journal was kept to document thoughts and feelings to recognize, acknowledge, and mitigate the influence of her role as a researcher and as someone with lived experience as an informal caretaker for a parent. Interview data were analyzed by the same author using thematic analysis as described by Braun and Clarke [67,68], beginning with several thorough readings of participant verbatim content to familiarize the researcher with the data and the identification of significant statements relating to the phenomenon under investigation [69]. Next, significant statements were placed into initial categories and organized into broader themes and subthemes. Themes and subthemes were reviewed, redefined, renamed, and explored as needed until no new themes emerged from the data.

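### The PDC formula as written is a possession ratio: it sums all supply dispensed, so it lacks the protection against early refills for which PDC was chosen

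*Protocol article*

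**What the plan says.** Under Medication Adherence via Proportion of Days Covered, the protocol article obtains pharmacy records "in order to obtain the average adherence of each participant over 5 cycles of OAAs". It takes its definition of PDC from a cited source, which adds up what was dispensed: "supply for all fills of a given drug in a particular time period, divided by the number of days in the time period". The next sentence gives the reason for choosing PDC over the alternative, namely that the "medication possession ratio can overestimate adherence for patients who refill their prescriptions early".

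On use, the same section states that "PDC will be assessed as the mean PDC for each group", and the Data Analysis section compares the two arms at study completion: "For PDC, independent sample 1-tailed" t tests. Data Analysis also correlates PDC with the self-reported MARS-5 score (Spearman).

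Two features of the Medication Reminders section bear on the point. The reminder templates are "tailored to a 21-day cycle (14 days on per 7 days off) or a 28-day cycle (21 days on and 7 days off"), so both regimens have scheduled days without drug. At the end of each cycle, "users receive a notification prompting them to refill their prescription and reload the 21-day or 28-day cycle template".

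**The concern.** The name of the measure, the reason for choosing it and its formula cannot all stand. A proportion of days covered counts each day in the window once, as covered or not, so it cannot exceed 100%. The printed numerator instead adds up everything dispensed. When a refill is collected before the previous supply runs out, the overlapping days are added a second time. Supply that runs past the end of the window is added too. Nothing else in the article removes overlap, carries early supply forward or sets a maximum.

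This matters because PDC is the article's objective measure of adherence. An analyst who follows the formula would score early refilling as extra adherence, the fault the article attributes to the rejected measure. That score would then feed a comparison of means and a correlation.

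**Working it through.** The article gives no PDC value, expected mean or PDC-based sample size, so there is no stated figure to reproduce. The check applies the printed formula to example refill histories and compares it with distinct days covered.

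**Inputs from the article**
- Window: 5 cycles, i.e. 5 × 28 = 140 days or 5 × 21 = 105 days.
- Final sample: 23 in the experimental group and 18 in the control group (Results).

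**Assumptions not in the article**
- Each fill is recorded as one full cycle of supply (relaxed at the end).
- Refill timing is illustrative.

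**Formulas**
- Written formula: (number of fills × days' supply per fill) / days in window.
- Distinct days covered: (days in window with drug on hand, each counted once) / days in window. Overlapping supply is either lost (overlap counted once) or moved to the end of the previous supply (carry-forward).

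**1. Refilling on time, 28-day cycles.** Fills on days 0, 28, 56, 84 and 112: 5 × 28 / 140 = 100%. Distinct days: 100%. The two agree.

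**2. Refilling 3 days early each time.** Fills on days 0, 25, 50, 75, 100 and 125: 6 × 28 / 140 = 168 / 140 = 120%. Distinct days: 140 / 140 = 100%. The surplus of 28 days is 5 × 3 = 15 overlapping days plus 125 + 28 − 140 = 13 days beyond the window.

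**3. Other early patterns.**

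| Cycle / window | 3 days early | 5 days early | 7 days early | Distinct days |
|---|---|---|---|---|
| 28 / 140 days | 6 × 28 / 140 = 120% | 7 × 28 / 140 = 140% | 7 × 28 / 140 = 140% | 100% throughout |
| 21 / 105 days | 6 × 21 / 105 = 120% | 7 × 21 / 105 = 140% | 8 × 21 / 105 = 160% | 100% throughout |

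**4. Early refills followed by a gap.** 28-day fills on days 0, 21, 42, 63 and 119.
- Written formula: 5 × 28 / 140 = 100%.
- Overlap counted once: days 0 to 90 (91 days) plus days 119 to 139 (21 days) = 112; 112 / 140 = 80%.
- Carry-forward: 4 × 28 = 112 days plus the same 21 = 133; 133 / 140 = 95%.

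This value stays within 100%, so a cap alone would not reveal the error.

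**5. Effect on an arm mean.** One extra 28-day fill adds 28 / 140 = 20 points for that participant, which is 20 / 23 = 0.9 points on the experimental mean, or 20 / 18 = 1.1 points on the control mean.

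**6. If recorded supply is dosing days only (21 of 28).** Five fills give 5 × 21 / 140 = 75%, six give 126 / 140 = 90% and seven give 147 / 140 = 105%. Exceeding 100% then takes seven fills. On this recording a fully adherent participant scores 21 / 28 = 75% or, on the other template, 14 / 21 = 67%.

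**The case against.** **A copying slip.** The definition is given as a quotation from a source, with a closing quotation mark visibly out of place. The name of the measure and the reason for choosing it show what was intended, and covered days may in fact have been used. This is plausible but cannot be confirmed from the article. Nor does it remove the defect, because the article states an explicit numerator and that numerator contradicts the next sentence.

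**Detail left to a fuller document.** Carry-forward, truncation and capping rules are commonly left to an analysis plan, and their absence alone would not be a finding. The finding is the stated formula, which a later plan following it would inherit.

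**Values above 100% depend on recording.** This stands. The 120% to 160% figures assume full-cycle supply per fill; with dosing-day supply, six fills stay at 90%.

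**Bias towards the experimental arm.** A reader might infer that, because only the experimental group has access to refill prompts, the formula inflates adherence in that arm and pushes the 1-tailed test towards the hypothesis. The article does not support this. The prompt comes at the end of a cycle, which favours refilling on time, and on-time refilling scores the same under both calculations in case 1. Reminders are also optional, and no refill timing by arm is reported.

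**Small consequences.** This largely stands. One participant moves an arm mean by about a point. PDC is one of several aim 3 outcomes in a pilot whose primary outcomes are feasibility and acceptability, and the sample size rests on a repeated-measures ANOVA of other outcomes.

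**Conclusion.** The point holds as an internal contradiction. The PDC formula is a possession ratio and has the weakness for which the article sets the medication possession ratio aside. With full-cycle recording and a 140-day window, one extra fill yields 120% instead of at most 100%, worth 20 points for the participant and about 0.9 points on a 23-person mean. A gap in coverage can also disappear, with 100% reported for 80% covered (95% with carry-forward). How many participants refilled early, and how pharmacies recorded days' supply, are not given, so the total effect on either arm is unknown.

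The error would enter both the t test and the correlation with MARS-5. It should be corrected, but it does not undermine the pilot's primary aims. The documents show neither a bias in favour of the intervention nor that the wrong calculation was carried out.

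**What to change.** Redefine PDC as the number of distinct days in the observation window with drug available, divided by the days in that window. State that overlapping supply is carried forward to the end of the previous supply, that supply beyond the window end is ignored, and that the maximum is 100%.

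Treat scheduled off-days the same way in numerator and denominator, for example by counting a dispensed cycle as covering its full cycle length. Otherwise, where supply is recorded as dosing days, fully adherent participants would score 75% or 67% according to their regimen.

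If the written formula is kept, call it the medication possession ratio and delete the claim about early refills.

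The cost is a corrected definition and a short recalculation from the pharmacy records already sought, provided they hold fill dates and quantities. The article says results were still to be published, so the definition could be settled before they are reported.
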